## Abstract

**Introduction::**

Inappropriate polypharmacy is prevalent among patients with chronic kidney disease (CKD), and can be mitigated by deprescribing. We aim to evaluate the clinical and economic impact of a multidisciplinary deprescribing programme in Qatar’s healthcare system.

**Methods::**

This randomised controlled trial will be conducted at ambulatory dialysis centres, with an internal pilot to assess the feasibility of recruitment, intervention implementation, and safety measures. Patients will be randomised to usual care or an intervention group where a clinical pharmacist, in collaboration with a multidisciplinary healthcare team, will deliver a structured deprescribing intervention, including periodic monitoring over six months. Outcomes will be measured at baseline, three, and six months. The primary outcome is the proportion of patients with at least one potentially inappropriate medication (PIM). Secondary outcomes include pill burden, treatment burden, hospitalisations, emergency department visits, quality of life, and adherence. A cost–benefit analysis will also be performed. A total of 250 patients provides 90% power to detect a 50% reduction in PIM prevalence (α = 0.05). The statistical analysis will be based on the intention-to-treat principle, using mixed-effects models to account for repeated measures.

**Discussion::**

Findings will provide novel evidence on deprescribing in CKD, informing future clinical and policy interventions.

**Trial Registration:**

ClinicalTrial.gov. NCT06324045. Registered on 15 March 2024.

## Introduction

Chronic kidney disease (CKD) is a major global public health problem, with an estimated 11.7–15.1% of the global population affected.(Lv & Zhang, 2019) Patients with CKD often experience multiple complications and comorbidities, including cardiovascular diseases (CVDs), anemia, diabetes, and thyroid disorders (Fraser et al., 2015). The management of CKD typically leads to polypharmacy, as most disease management approaches and clinical practice guidelines often address these comorbidities and complications in isolation, rather than considering their interrelatedness (Fraser et al., 2015; George et al., 2021; Manski-Nankervis et al., 2021).

Polypharmacy can often be inappropriate, and it is associated with several adverse consequences on patient health outcomes (Johansson et al., 2016). These consequences include, but are not limited to, deterioration in quality of life, increased hospitalisations, falls, and higher mortality rates (Ernst et al., 2020). Inappropriate polypharmacy is particularly prevalent among patients with CKD (Triantafylidis et al., 2018). For example, a study found that 45% of old veterans in the US with kidney disease were prescribed one or more inappropriate or incorrectly dosed medications (Chang et al., 2015). Similarly, in Qatar, where approximately 13% of the population suffers from CKD (Reddy & Cho, 2016), a pharmacoepidemiologic study reported that 75% of older adults were prescribed five or more medications (Al-Dahshan et al., 2020). Moreover, medication-related burden has been linked to decreased medication adherence among older adults in Qatar (Zidan et al., 2018).

A prospective, cross-sectional study was conducted to assess treatment-related burden and health-related quality of life (HR-QOL) among 280 patients diagnosed with CKD at a tertiary care kidney centre in Qatar (Al-Mansouri et al., 2021). Nearly one-third of the participants, especially those receiving hemodialysis, reported a moderate to high treatment-related burden. HR-QOL scores were significantly lower in patients receiving hemodialysis (HD) compared to those who were pre-dialysis. The study highlighted the negative impact of higher treatment-related burden on the patient’s quality of life. The investigators recommend that healthcare systems and clinicians account for this burden when developing CKD management strategies. Some of these strategies could include medication reconciliation and deprescribing (Al-Mansouri et al., 2021).

Deprescribing is a proactive intervention designed to minimise the adverse consequences of inappropriate polypharmacy (Reeve et al., 2017). It involves the supervised process of stopping a medication, reducing its dose, or replacing it with a safer alternative in order to improve patients outcomes and reduce adverse drug events (ADEs) (Gazarin et al., 2020). Several studies have demonstrated the safety and potential effectiveness of deprescribing in improving quality of life and medication adherence, as well as reducing ADEs, mortality rates, and potentially inappropriate medications (PIMs) (Gazarin et al., 2020; Page et al., 2016; Reeve et al., 2017; Romano et al., 2022; Thio et al., 2018). Inappropriate polypharmacy also places a burden on healthcare systems, incurring additional costs from managing the associated ADEs. Implementing deprescribing programmes can help reduce these costs, including those related to admissions due to ADEs and unnecessary drug therapy (Hurley et al., 2024; Kemp et al., 2011; Kutner et al., 2015; Scott et al., 2015).

Although deprescribing protocols and guidelines are now widely available (Manski-Nankervis et al., 2021; Reeve, 2020), their implementation in clinical practice remains limited (Farrell et al., 2015; Scott et al., 2017). Deprescribing is rarely implemented in clinical practice due to several barriers (Okeowo et al., 2023), including a lack of awareness among healthcare providers (Doherty et al., 2020), limited time during consultations (Doherty et al., 2020), insufficient training on deprescribing protocols (Doherty et al., 2020), and resistance from patients who may be hesitant to discontinue long-term medications (Okeowo et al., 2023). Furthermore, there is still a need for robust studies to provide strong evidence of the impact of these programmes on various health outcomes (Rankin et al., 2018). Given the high prevalence of polypharmacy among patients with CKD, there is an urgent need to implement and evaluate promising strategies such as deprescribing for this population (Manski-Nankervis et al., 2021; Triantafylidis et al., 2018). We believe deprescribing is a prudent and innovative intervention that could yield significant clinical and economic benefits if effectively integrated into the Qatar healthcare system. We hypothesise that patients with stage 5 CKD, especially those receiving HD or managed in low-clearance clinics, represent ideal candidates for deprescribing interventions.

The aim of the current study is to conduct an RCT, including an internal pilot, to compare the clinical outcomes and cost–benefit of a multidisciplinary team-delivered deprescribing intervention with usual care. This study represents the evaluation stage of a larger programme, divided into multiple stages, following the Medical Research Council (MRC) guidance on the development and evaluation of complex interventions (Skivington et al., 2024).

## Methods and analysis

### Study design

This is a pragmatic, multicenter, randomised controlled trial (RCT) with a parallel-group design and an embedded internal pilot. It is being conducted in ambulatory dialysis centres at Hamad Medical Corporation (HMC) to evaluate the effectiveness of a multidisciplinary team-delivered deprescribing intervention on clinical, humanistic, and economic outcomes. The internal pilot aims to assess the feasibility of recruiting a sufficient number of CKD patients, providing the intervention components effectively, and ensuring that there are no safety concerns associated with the intervention. The study is currently recruiting participants and is expected to be completed by 2026. Figure 1 illustrates the overall study design.

**Figure 1. F0001:**
[figure not shown]
Flowchart of the proposed randomised controlled trial.

### Study participants

The study population includes patients with CKD who have regular follow-up appointments at any HMC-affiliated kidney centre. Patients with CKD undergoing HD three times per week and pre-dialysis patients with low renal clearance who attend monthly follow-up appointments will be recruited for the study. Individuals with eGFR < 15 mL/min/1.73 m^2^, who have not yet reached the threshold for HD are usually managed in these clinics. Patients who require HD but have declined the procedure will not be included in the study.

#### Inclusion criteria

Patients diagnosed with kidney failure (KF), receiving HD treatment or pre-dialysis patients (eGFR <15 mL/min/1.73 m²) attending a low clearance clinic.Patients receiving care at one of the ambulatory kidney centres in Qatar for at least two months.Patients able to communicate in Arabic and/or English.

#### Exclusion criteria

Life expectancy of less than 6 months.Unstable or have a diagnosed psychiatric condition.Exhibiting uncontrolled or exit-seeking behaviours (e.g. attempting to leave the premises due to confusion, frustration, or anger).Critically-ill patients, pregnant women, children, individuals with mental illness, dementia, and unconscious patients.

### Study setting

The study setting is the ambulatory dialysis centres in Qatar, which are operated by HMC. The centres include Fahad Bin Jassim, Al-Wakrah, Shahania, and Alshamal Kidney Centres, which provide dialysis and pre-dialysis care for Qatari nationals and other residents of Qatar with CKD. In addition to dialysis services, the centres also offer outpatient pre-dialysis care for patients with advanced CKD. In addition, different specialty teams, including cardiology, endocrinology, vascular surgery, and psychology, provide consultations and care for the patients at these facilities.

### Recruitment

CKD patients are screened for eligibility through medical records. Eligible patients are invited to participate during their routine visits to an ambulatory kidney centre in Qatar. To ensure feasibility and practicality, selecting patients follows a non-probabilistic approach, recruiting consecutive cases as they become available. Recruitment interaction happens at the beginning or end of the appointment times to minimise disruptions and avoid additional burden to patients while receiving treatments. The recruitment process is performed by trained research assistants.

### Study groups

The study comprises two groups: (1) Control arm: Patients who receive usual (i.e. standard) ambulatory care. This entails monthly medication reviews conducted as part of routine care, mainly by the nephrologist and in-charge nurses. Moreover, any issues highlighted by the patients or the care team are addressed by the attending physician or referred for necessary consultations. The pharmacist's role in these rotations is limited and occasional, with limited MDT discussions including the patient's medications. Importantly, the setting is no different than other HD and clinic settings where usually the changes of the medications are subject to present complaints or apparent health problems; (2) Intervention arm: Patients who receive a structured deprescribing intervention delivered by the multidisciplinary team during their patient daycare visits at the centre.

### Randomisation, blinding, and allocation concealment

After obtaining informed consent, patients are randomised into one of the two study arms. Each recruited patient is assigned a unique code. Randomisation is stratified by dialysis dependency (dialysis vs. pre-dialysis) using randomly permuted balanced block varying block sizes to maintain allocation concealment.. The anticipated recruitment distribution is approximately 4:1 (dialysis: pre-dialysis), reflecting the underlying patient population at the study sites. The allocation sequence was generated by a separate computer and kept concealed from all research personnel. Once a patient is recruited and baseline data are collected, the assigned code is given by the responsible research assistant. Given the nature of the intervention, neither the healthcare provider delivering the intervention nor the patients can be blinded to the group allocation. To avoid contamination, the MDT-CKD physicians interact only with the participants in the intervention group.

### Deprescribing intervention and workflow

The proposed deprescribing workflow consists of the following stages:
Patient assessment: Upon recruitment, the patient’s information is collected through participant interviews and electronic medical records (via Cerner). These include sociodemographic, clinical, and medication information. Additionally, patients complete self-reported questionnaires to assess medication adherence, treatment burden, and quality of life.Deprescribing plan development: For patients in the intervention group, the clinical pharmacist highlights the potentially problematic medications, drafts a deprescribing plan for each, consult the multidisciplinary team and the relevant specialists, and documents in the patient’s medical records. The potentially problematic medications are identified through the Medication Appropriateness Index (MAI) tool, and the deprescribing plans are drafted using deprescribing algorithms adapted from evidence-based deprescribing guidelines in the CKD setting (Zidan et al., 2025). Validation of these algorithms was conducted through input from an expert panel and piloted during the pilot RCT. The results of the validation and piloting are not yet published. The intervention targets all PIMs as we intend to provide a holistic approach. Prioritising the deprescribing plans is based on patient safety and medication properties. Only one medication is targeted per deprescribing cycle, unless deemed clinically appropriate. These are decided on case-by-case basis during the MDT-CKD meetings.Implementation and monitoring of the deprescribing intervention: The team implements and monitors the approved deprescribing plan during the patient’s appointments at the centre or through follow-up phone calls, as applicable. The team periodically reviews the intervention’s progress, discussing results and addressing any issues to take corrective actions. Monitoring protocols are tailored per medication class as per the clinical guidelines.Deprescribing plan finalisation: During subsequent appointments, the medication plan is reconciled and discussed with the patient. Patients are provided with a deprescribing card, containing updated medication information to ensure clear communication and adherence to the revised regimen.Post-deprescribing follow-up: For each deprescribing plan, the MDT-CKD clinical pharmacist conducts three follow-up interviews or phone calls with the patients on days 2, 7, and 28 post-deprescribing. These follow-ups are designed to monitor late-onset withdrawal symptoms and to address any questions or concerns raised by the patient. Any changes to the patient’s medication regimen are documented and discussed with the multidisciplinary team to ensure appropriate management.Documentation: All deprescribing processes and decisions related to each medication are documented in the participant’s medical records. For process evaluation, a checklist detailing each step of the deprescribing process is completed for every participant to ensure the fidelity of the intervention.

### Risk mitigation strategy

Although deprescribing is generally considered safe, both expected and unexpected risks will be managed in accordance with IRB SOP-09, which requires immediate reporting, review by the IRB, and corrective action if necessary. Furthermore, the deprescribing follow-up protocol was designed to actively monitor for immediate and late-onset adverse drug withdrawal events (ADWEs). Before plans implementation, anticipated risks are communicated to patients, and the monitoring plan is tailored accordingly. If an ADWE occurs, the deprescribing process may be slowed, modified, or discontinued depending on the specific medication, clinical plan, and patient response. In all cases, patients are provided with the direct contact numbers of the clinical team to report any concerns or sudden symptoms.

### Outcome measures

Outcomes will be assessed at different time points (baseline, 3, and 6 months) and compared between the two participant groups.

#### Primary outcome

***Potentially inappropriate medications (PIMs):*** This is represented as the number of events and non-events in each study group. It will also be reported as the percentage of participants with PIMs. PIMs are defined as drugs for which use should be avoided due to high risk of adverse reactions and/or insufficient evidence of benefit when safer and equally or more effective alternatives are available for this population (Fick et al., 2003). This will be determined through medical records using the MAI tool (Hanlon & Schmader, 2013). This implicit tool helps clinicians in making a comprehensive assessment of medication appropriateness. It contains 10 items to assess the appropriateness based on indication, efficacy, correct dosage, correct directions, practicality of the directions, interactions, duration of therapy, and costs. The medication is considered a PIM if the MAI score is ≥1. The MAI tool was deemed appropriate to identify PIMs among the target population as it provides a comprehensive overview of the prescribed medications. It has previously been used to identify PIMs among CKD patients (Wubshet H Tesfaye et al., 2019). In our assessment, the costs are not considered, given that the healthcare provider in Qatar (HMC) governs the decisions regarding the purchase of medication brands. Consequently, it was impractical for the research team to compare all medication alternatives (as the item of the cost mentioned in the MAI tool).

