### Data collection instruments

*Data collection form:* An Excel sheet was developed to collect demographic and clinical data and outcome measures. It contains participants’ characteristics, medical history, comorbidities, prescription information, laboratory data, and patient-reported outcomes.*Treatment Burden Questionnaire (TBQ):* The instrument’s responses are rated using a Likert-type scale ranging from 0 (not a problem) to 10 (a big problem). The TBQ global score is calculated by summation of each item score, with a maximum score of 150 points. The scores are further categorised as low burden (0–50), moderate burden (51–99), and high burden (100–150) (Tran et al., 2014).*Kidney Disease Quality of Life (KDQOL™) questionnaire:* The KDQOL-36^TM^ consists of five dimensions: Physical Component Summary (PCS), Mental Component Summary (MCS), Burdens of Kidney Disease (BKD), Symptoms and Problems of Kidney Disease (SPKD), and Effects of Kidney Disease (EKD). Numeric items are transformed into a 0–100 points scale, with total possible scores ranging from 0 to 3600 (higher scores indicate better quality of life) (Hays et al., 1994).*Adherence to Refills and Medications Scale (ARMS):* This is a 12-item medication adherence assessment tool with proven reliability and validity that was developed in English language and translated into several languages including Turkish,(Gökdoğan & Kes, 2017) Korean,(Kim et al., 2016) Chinese,(Chen et al., 2020) Polish,(Lomper et al., 2018) and Arabic.(Alammari et al., 2021; Zidan et al., 2018) The total scores range from 12 to 48, with higher scores indicating poor adherence (Kripalani et al., 2009).

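### The primary outcome is a judgement score taken from medical records that, for intervention patients, also hold the deprescribing plan and decisions, and no masked scorer is described

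*Protocol article*

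**What the plan says.** Four parts of the protocol article bear on this.

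- **Primary outcome, source and tool.** The outcome is described thus: "This will be determined through medical records using the MAI tool". Of the MAI it says: "This implicit tool helps clinicians in making a comprehensive assessment of medication appropriateness". The threshold is low: "The medication is considered a PIM if the MAI score is ≥1". The abstract defines the endpoint per patient, as having at least one PIM.
- **Deprescribing intervention and workflow.** The intervention works from the same tool: "The potentially problematic medications are identified through the Medication Appropriateness Index (MAI) tool". This is done in one arm only: "For patients in the intervention group, the clinical pharmacist highlights the potentially problematic medications, drafts a deprescribing plan for each". The plan is entered in the patient's medical record, and the documentation step repeats this for everything that follows: "All deprescribing processes and decisions related to each medication are documented in the" participant's medical record.
- **Randomisation, blinding, and allocation concealment.** Because of the nature of the intervention, "neither the healthcare provider delivering the intervention nor the patients can be blinded to the group allocation". The section does not mention whoever scores the outcome.
- **Data collection instruments.** A separate data collection form holds, among other things, "medical history, comorbidities, prescription information, laboratory data, and patient-reported outcomes".

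**The concern.** The MAI asks a clinician to judge each drug, and a single flagged item on a single drug makes the patient an event. An outcome of this kind is sensitive to what the scorer knows. A scorer who opens an intervention patient's record finds a plan built on the same index and an account of what was decided about each drug. A control record has no such plan: usual care consists of monthly medication reviews, mainly by the nephrologist and nurses, with little pharmacist input. The source therefore reveals the arm and also shows one side's reasoning about appropriateness.

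The reason given for not blinding providers and patients is sound for them, but it does not apply to someone scoring a drug list. The other safeguards do different work. The separate team, and keeping it unaware of the hypothesis, guard against contamination. The concealed sequence and varying blocks protect allocation.

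At stake is the interpretation of the main result. A fall in PIMs because flagged drugs were stopped is the intended effect. A fall because remaining drugs were judged more leniently in one arm is not. If scoring is unmasked, the two cannot be told apart in the scores so obtained.

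**Working it through.** **Inputs from the Sample size section:** PIM proportion 40% in controls; target relative decrease of 50%, so 20% with the intervention; two-sided α 5%; power 90%; 106 per group before dropout; 125 per group enrolled; 10% dropout.

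**Reproducing the plan's figure.** Two proportions, normal approximation, unpooled variance:

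n = (1.960 + 1.282)² × (0.40×0.60 + 0.20×0.80) / 0.20² = 105.07, rounded up to 106 per group. This matches the article, so 40% and 20% are the working proportions.

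**Illustration of scoring bias.** Take no true effect, with 40% in both arms. With 10% dropout, 125 × 0.90 = 112.5, so use 112 per arm. Let m be the share of intervention patients with a PIM who are wrongly scored as free of one. The documents give no value for m, so each one below is an assumption. The recorded intervention proportion is 0.40 × (1 − m), and the apparent rate ratio is 1 − m.

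z = (0.40 − p₂) / √[(0.24 + p₂(1 − p₂)) / 112]

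Chance of a significant result favouring the intervention = P(Z > 1.96 − z)

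| m (assumed) | recorded p₂ | z | false success |
|---|---|---|---|
| 0% | 0.40 | 0 | 2.5% |
| 5% | 0.38 | 0.02/√(0.4756/112) = 0.31 | about 5% |
| 10% | 0.36 | 0.04/√(0.4704/112) = 0.62 | about 9% |
| 20% | 0.32 | 0.08/√(0.4576/112) = 1.25 | about 24% |
| 25% | 0.30 | 0.10/√(0.4500/112) = 1.58 | about 35% |

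At m = 50% the recorded proportion would be 20%, which is the whole planned effect.

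**Cross-check.** A pooled two-sided test, counting rejections in either direction (nominal 5%), gives 6.1%, 9.4%, 23.8% and 34.7% at 112 per arm for the same four shares. At 106 per arm it gives 6.0%, 9.2%, 22.8% and 33.2%.

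**Sensitivity to prevalence.** Any drug scoring 1 or more counts, so prevalence could exceed 40%. If it were 80% (an assumption), the two-sided rejection rate at 112 per arm would be 11.1% for m = 5% and 28.8% for m = 10%.

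These are simple comparisons of two proportions, not the adjusted Poisson regression that the article plans. They show the order of size, not a forecast.

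**The case against.** The strongest reply is that part of this rests on silence. The article names neither the scorer nor the scorer's masking, it condenses a longer protocol, and naming medical records may only identify the data source. Scoring from data extracted onto the form would fit the text. That stands, and it limits confidence to medium. It does not dispose of the point, because the article itself fixes a judgement tool, the record as source and arm-revealing content in that record. Its blinding section then stops at providers and patients.

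The assumed shares can also be challenged. To clear a patient wrongly, a scorer must rate every remaining drug as having no fault, and a drug that was stopped is simply no longer on the list. The share could be small, which is why the table starts at 5%.

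Several stronger readings are tempting but not supported:

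- *The intervention pharmacist scores the outcome.* The article does not say so.
- *Using one tool both to target and to measure is itself a flaw.* It is legitimate. The difficulty is the shared tool together with judgement scoring and notes that reveal the arm.
- *The baseline score differs by arm because the pharmacist's MAI review follows allocation.* The randomisation section has baseline data collected before the assigned code is given, and nothing says that the pharmacist's review supplies the baseline value.
- *The bias is beyond repair once the data are in.* Stored data can be rescored under masking.

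**Conclusion.** The point holds in limited form. Scoring as the article describes it, from the unredacted record, exposes the scorer to the arm, and no masked or independent scorer is described. The likely direction favours the intervention and the size is unknown. Under the assumed shares of 5% to 25%, with no true effect and 40% prevalence, the chance of false success rises from 2.5% to between about 5% and 35%. A reader might infer that the effect will be produced by scoring. The documents support only that scoring could produce or enlarge it. The change should be made. If the full protocol already provides masked scoring, one sentence in the article settles the matter.

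**What to change.** Score the MAI for both arms at baseline, month 3 and month 6 from the existing data collection form. Export the prescriptions, comorbidities and laboratory data under the study code, without arm, deprescribing-team notes or deprescribing documentation, and present patients and visits in mixed order. Use an existing research-team member who is outside the MDT-CKD and did not handle allocation. Recruitment is under way, so rescore completed visits in the same way before analysis. State the procedure in the blinding section.

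The cost is a coded export of data already collected and a rule about which member of staff scores. Sample size, visits and patient care are unchanged. There are two downsides. Some record context is lost, mainly in the intervention arm, and items such as indication, directions and duration may depend on it, so check first that the form captures what they need. Drug changes visible across visits may also still hint at the arm; mixed ordering reduces this but does not remove it.
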